#### Exploratory Outcome Measures

In addition, we want to untangle the effects of possible biomarkers and predict treatment outcomes, including cardiovascular risk factors (waist:hip ratio, ankle arm index [a measure to determine peripheral atherosclerosis], c-reactive protein, triglyceride, high-density lipoprotein cholesterol, total cholesterol, and glycated hemoglobin levels); neurophysiological biomarkers, that is, using heart rate reduction, heart brain coupling, and an increase in heart rate variability; magnitude and angle of the electric field induced by rTMS in the cortex; structural and functional brain networks as biomarkers for clinical response; effects of cortical depth; and structural and functional brain network changes induced by 10 Hz rTMS and PAiT (and their relation to treatment outcome), as measured by structural and functional MRI.

We also aim to assess changes in emotional and cognitive task performance (Hariri [26,27] and Tower of London [28]) and task-related brain activation induced by 10 Hz rTMS and PAiT (and their relation to treatment outcome), as measured by task-based functional MRI; assess the changes in Pavlovian bias induced by 10 Hz rTMS and PAiT (and their relation to treatment outcome), as measured by a behavioral controllability task (RobotMadness, refer to Dorfman et al [29] for more information regarding controllability and Pavlovian biases); and to establish a biobank to determine standard 10 Hz rTMS– and PAiT-induced changes, as measured with blood derived biomarkers. Markers of interest include brain-derived neurotrophic factor and epigenetic changes for rTMS-induced plasticity, genotyping for treatment response prediction.

### Blinding

Participants and those who will be administering the rTMS or PAiT treatment cannot be blinded. Those carrying out clinical assessments will be blinded. Blind rating will be carried out via video-recorded interviews with participants. Interviewers will not be blinded to the treatment conditions and, therefore, will be thoroughly instructed to carry out the interview in a structured and objective manner. A blinded rater will score the videotaped clinical assessments. To ensure minimal bias effects, 20% (227/1134) of interviews will be randomly assessed on interrater reliability and interview quality. All video footage will be deleted after rating the interviews and after the independent monitor has reviewed and agreed. The clinical ratings will be stored for further analysis.

### Sample Size Calculations

Our trial should consist of 108 patients (for a 2‐sided test at α=.05 and with a power=0.80). Remission rates of patients treated with SNT in 2 open‐label studies and 1 interim analysis from an RCT were extremely high, that is, 79%. The remission rates in patients treated with ECT, the most well-known and effective treatment for TRD, is approximately 55% (range 48%‐65%). Our sample size calculation is based on the conservative assumption that our PAiT protocol is at maximum as effective as ECT in patients with TRD. For our sample size calculation, we used the 55% remission rate and the known remission rate for standard 10 Hz rTMS, 25%. We will oversample the necessary 82 patients with 32% to adequately handle possible attrition, as the new intervention will be relatively intense compared to standard 10 Hz rTMS treatment, resulting in a required sample size of 108 patients.

### Statistical Analyses

#### Overview

Statistical analyses will be performed on the intention‐to‐treat as well as the per protocol sample. Missing data will be replaced using the multiple imputation method. For all analyses, corrected *P* values of <.05 will be regarded as statistically significant. Safety data (eg, side effects) will be collected and summarized in the study results. A description of the analyses for the primary, secondary, and exploratory objectives is provided in the following sections.

#### Primary Study Parameters

For the intention‐to‐treat analysis, we will use a chi-square test to determine differences in remission 1 week after treatment.

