### Setting of the Study

This multicenter trial will take place within the Dutch specialized mental health care setting. Patients will be recruited from specialized outpatient clinics with ample experience in both the treatment of TRD and treatment with rTMS or iTBS, through self‐referral, and through the patient organization for depression (refer to the CONSORT [Consolidated Standards of Reporting Trials] flowchart in Figure 1)*.* Participating outpatient clinics are Radboudumc, GGZinGeest, Maastricht University Medical Centre+, and Amsterdam University Medical Centre. The following rTMS machines are used in this trial: MagStim Rapid2 (Amsterdam University Medical Centre, GGZinGeest, and Radboudumc), Neurosoft Neuro-MSX (Radboudumc), MAG and more powerMAG (GGZinGeest), and MagVenture MagPro X-100 (Maastricht University Medical Centre+). All sites use figure-of-8 coils. Localite is used for neuronavigation at all sites. The Neurosoft Neuro-MSX uses a built-in neuronavigation software.

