### Participants

We aim to include 108 adult patients diagnosed with moderate to severe (Hamilton Depression Rating Scale >16) unipolar major depressive disorder without psychotic symptoms and who have had a failed response to at least 2 treatment trials with adequately dosed antidepressants or evidence-based forms of psychotherapy (interpersonal therapy, cognitive behavioral analysis system of psychotherapy, behavioral therapy, cognitive behavioral therapy, cognitive bibliotherapy, problem‐solving therapy, brief psychodynamic therapy, and reminiscence therapy). Exclusion criteria include lifetime diagnosis of bipolar disorder, current psychotic disorder, substance abuse disorder, suspected dementia, active suicidal thoughts with intent to act on them, patients with epilepsy, patients with large or ferromagnetic metal parts in the head (except for a dental wire), implanted cardiac pace maker or neurostimulator, or inability to understand or comply with study requirements.

These exclusion criteria serve 2 purposes: first, to ensure a clinically homogeneous sample of patients with unipolar depression, free from comorbid conditions that could affect treatment effectiveness; and second, to comply with safety guidelines related to rTMS, the accelerated iTBS protocol, and the required magnetic resonance imaging (MRI) procedures, as well as general safety standards.

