### Randomization

Participants will be randomly assigned to either the rTMS or the PAiT arm. Randomization will be done via Castor EDC and will be stratified for treatment center. We will use block randomization using random sequences of block sizes of 2, 4, and 6. This approach ensures treatment assignment balance within each complete block and minimizes the imbalance of group sizes within clinical centers, thus correcting for confounding from possible differences between treatment sites (such as differences in experience with rTMS). In addition, before the start of the trial, we will note patient’s preferred treatment, that is, standard 10 Hz rTMS or PAiT. The expected study duration is 48 months, and inclusion of patients started in February 2024.

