### Outcome Measures

#### Main Study Parameter or End Point

Remission of depression 1 week after the last treatment session was defined as a score of ≤7 on the 17-item Hamilton Depression Rating Scale (HDRS‐17).

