### Relevance for Practice

PAiT can be applied in various treatment settings and by various health care professionals. If positive, the results of our study will provide Dutch and international professionals with an adequately powered trial answering whether PAiT is an evidence‐based therapy for depression. A novel therapy is necessary to overcome TRD in patients who did not respond after 2 or more evidence‐based treatments. In addition, this trial will provide further insights into the differences in the side effects, long-term effects, and (factors contributing to) possible relapse between rTMS and PAiT.

Different rTMS equipment will be used at different sites in this trial. Technical and practical differences in the equipment may introduce variability across sites. However, using different machines is important for generalizability of the results because, in daily practice, mental health institutions use different rTMS machines. To minimize variability in the practical application of rTMS, we thoroughly instruct technicians to follow our provided training and standard operating procedures. All treatments will be conducted using neuronavigation systems with a calibration accuracy of less than 3 mm. In addition, we will control for rTMS machine or site to ensure the reliability of our analyses and investigate the impact of different equipment.

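### The primary remission test is an unstratified chi-square, although randomization is stratified by center and control for site is promised; no described remission analysis carries that control

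*Protocol article*

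**What the plan says.** All places are in the Protocol article.

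- **Primary analysis** (Primary Study Parameters). For the intention-to-treat sample, "we will use a chi-square test to determine differences in remission 1 week after treatment". No stratum, covariate or model is named. The endpoint is binary: "Remission of depression 1 week after the last treatment session", defined as an HDRS-17 score of 7 or less.
- **Randomization.** It "will be stratified for treatment center", with "random sequences of block sizes of 2, 4, and 6". No other stratification factor is listed. The section credits the stratified blocking with correcting for confounding by site, and gives differing rTMS experience as an example of a site difference.
- **Centers** (Setting of the Study). There are four: "Participating outpatient clinics are Radboudumc, GGZinGeest, Maastricht University Medical Centre+, and Amsterdam University Medical Centre".
- **Machines** (same section). "MagStim Rapid2 (Amsterdam University Medical Centre, GGZinGeest, and Radboudumc), Neurosoft Neuro-MSX (Radboudumc), MAG and more powerMAG (GGZinGeest"), and a MagVenture device at Maastricht.
- **Control for site** (Discussion, Relevance for Practice). "we will control for rTMS machine or site to ensure the reliability of our analyses". The sentence names neither the endpoint nor the method.
- **Other analysis of remission** (Secondary Study Parameters). The six-week comparison of remission is also a chi-square test.

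**The concern.** The trial expects its sites to differ. The Randomization section cites differing experience, and Relevance for Practice cites equipment. It stratifies by center for that reason and says that the analyses will control for machine or site. The one test fixed for the primary endpoint cannot do this, and neither can the other remission comparison.

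Two things follow. First, when randomization is balanced within centers and the test ignores centers, variation between centers stays in the error term, so the test is less sensitive than the design allows. Second, a reader cannot tell whether the site control is meant to touch the primary result, or whether the variable would be center or machine. Those choices should be fixed before outcome data are seen.

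**Working it through.** **1. Reproduce the planned sample size.** Inputs from Sample Size Calculations: remission 55% and 25%, two-sided alpha 0.05, power 0.80. Equal allocation is inferred from the balanced blocks. Mean rate = 0.40.

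n per arm = [1.960·√(2·0.40·0.60) + 0.842·√(0.55·0.45 + 0.25·0.75)]² / 0.30²
= [1.960·0.693 + 0.842·0.660]² / 0.09 ≈ 1.913² / 0.09 ≈ 40.7, so 41 per arm and **82** in total (power 80.3%).

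82 × 1.32 = 108.2, so **108**. Both figures reproduce. The sample size matches an unadjusted two-proportion test.

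**2. Tests compared.** Let a be the PAiT remitters, n1 and n0 the arm sizes, m all remitters and n the total. Subscript s marks a center.

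- Plain chi-square: (a − n1·m/n)² / [n1·n0·m·(n − m)/n³].
- Center-stratified Cochran-Mantel-Haenszel (CMH): [Σ(a_s − n1_s·m_s/n_s)]² / Σ[n1_s·n0_s·m_s·(n_s − m_s)/(n_s²·(n_s − 1))].

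**3. Simulation.** There were 6,000 runs per scenario, with four centers of near-equal size, permuted blocks of 2, 4 and 6 within center, and overall rates of 55% and 25% (25% in both arms for type I error). The documents give no between-center variation, so I assumed a logit SD of 0, 0.5 or 1.0. At 82 patients, the rTMS-arm rates by center are then 25% throughout; 14, 20, 28 and 38%; or 7, 15, 30 and 51%.

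| N | Logit SD | Type I error, plain | Type I error, CMH | Power, plain | Power, CMH | Change in power (points) |
|---|---|---|---|---|---|---|
| 82 | 0 | 4.6% | 4.6% | 81.7% | 80.7% | −1.0 |
| 82 | 0.5 | 4.0% | 4.5% | 81.9% | 82.5% | +0.6 |
| 82 | 1.0 | 3.6% | 5.0% | 83.0% | 86.8% | +3.8 |
| 108 | 0 | 5.0% | 5.2% | 89.1% | 89.2% | 0.0 |
| 108 | 0.5 | 4.7% | 4.9% | 89.7% | 91.0% | +1.2 |
| 108 | 1.0 | 3.4% | 5.3% | 91.5% | 94.3% | +2.8 |

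The simulation standard error of a single figure is about √(0.05·0.95/6000) = 0.3 points for type I error and √(0.82·0.18/6000) = 0.5 points for power.

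**4. Check by hand.** With arms balanced within centers, the plain test's variance is too large by the variance of the center rates. For rates of 7, 15, 30 and 51%, the mean is 25.75% and the variance is (18.75² + 10.75² + 4.25² + 25.25²)/4 = 280.7 squared percentage points, or 0.0281. The total binary variance is 0.2575·0.7425 = 0.191, so 0.0281/0.191 = 14.7% is between centers. The effective critical value is 1.960/√(1 − 0.147) = 2.12, which gives a two-sided type I error of about 3.4%. This agrees with the simulated 3.4% to 3.6%.

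**5. Adding baseline severity.** A separate simulation with 84 patients compared the chi-square with a linear risk-difference model on site and baseline HDRS with robust (HC3) standard errors. Its prognostic strengths were also assumed. Power was 0.88 against 0.84–0.85 with strong prognosis, 0.84 against 0.84–0.85 with moderate prognosis, and 0.79 against 0.83–0.84 with none. The logistic likelihood-ratio version had more power, but rejected in 5.5% to 6.4% of null runs. Baseline adjustment is therefore not a safe gain for the primary test at this size.

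**The case against.** The strongest reply is that the plan is not wrong. The chi-square is valid under stratified randomization, its type I error never rose above about 5%, and it matches the formula behind the 82. The Randomization section already assigns site confounding to the blocking. The sentence on machine or site stands in the Discussion, in a paragraph on equipment, and could refer to a supporting model set out in an analysis plan that is not shown. All of this stands, and it limits the size of the point. It does not tell the reader which remission analysis carries the control, and the test that the article does fix cannot.

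Some stronger readings are tempting but unsupported:

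- **Baseline severity as an ignored stratum.** Center is the only stratification factor. The severity threshold, "Hamilton Depression Rating Scale >16", is an eligibility criterion.
- **Two contradictory primary analyses.** Only Primary Study Parameters describes the primary analysis. The Discussion sentence does not name it.
- **Adjusting for machine would remove treatment effect.** That needs the machine to be chosen after randomization and to follow the arm. The documents say nothing on how or when a machine is assigned.
- **The chi-square blocks multiple imputation.** Naming a test does not prevent pooling of an effect estimate, and such detail may properly sit in the analysis plan.

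**Conclusion.** The point holds as a mismatch between design and analysis, with modest consequences. The primary test ignores the only randomization stratum, and no described analysis of remission delivers the stated control for machine or site.

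The plain test is conservative when centers differ; it is not invalid. A stratified test gains up to about 4 points of power at 82 patients and 3 at 108. Those upper figures need an assumed logit SD of 1.0 between centers. At 0.5 the gain is about 1 point, and with no center effect there is a loss of about 1 point at 82 and none at 108. The results also assume near-equal centers and a common treatment effect on the logit scale. It would be wrong to infer that the trial is underpowered or that its sample size must change.

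**What to change.** 1. In Primary Study Parameters, make the primary test of remission a Cochran-Mantel-Haenszel test stratified by center, reported with a center-stratified risk difference and 95% CI. Keep the plain chi-square as a sensitivity analysis.
2. In Relevance for Practice, state that the control is for center, the randomization stratum. Machine is not interchangeable with center: two sites have two machines each, and one machine type is shared by three sites. Examine machine only in a supporting analysis.
3. Optionally, prespecify a supporting regression of remission on arm, center and baseline HDRS-17, which is already collected. The ground is prognosis, not stratification.

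The change needs wording only, with no new data and no change to 82 or 108. The last posttreatment assessment is expected in January 2027, so it can be made before the analysis. The price is about 1 point of power at 82 patients if centers turn out not to differ.

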#### Secondary Study Parameters

The economic evaluations, that is, cost‐utility analysis, will be conducted in accordance with the Dutch guidelines for economic evaluations. The outcome measure for the cost‐utility analysis will be quality-adjusted life years, measured using the Dutch tariffs, that is, utility weights of the EQ‐5D‐5L [30-32]. Total costs will be estimated using a bottom‐up (or microcosting) approach, where information on each element of service used is multiplied by an appropriate unit cost and summed to provide an overall total cost. We will consider four types of costs: (1) intervention costs, (2) costs stemming from health care uptake, (3) patients’ and their family’s out‐of‐pocket costs, and (4) costs stemming from productivity losses due to absenteeism. The recall period for all resource use measurements will be 3 months. A baseline analysis will be performed to examine the comparability of groups at baseline in terms of costs and outcomes. If necessary, the methods will be applied to control for differences in baseline [33]. The incremental cost‐effectiveness ratio (ICER) will be computed to obtain the incremental costs per quality-adjusted life years gained. Stochastic uncertainty will be handled using 5000 nonparametric bootstraps and by plotting the simulated ICERs on the ICER plane. The bootstrap replications will be used to calculate the 95% CIs for the costs based on the 2.5th and 97.5th percentiles. For decision-making purposes, the ICER acceptability curve will be plotted for various willingness‐to‐pay ceilings. Missing data will be handled using single imputations nested in the nonparametric bootstrap samples [34].

For the patient‐reported outcome measures, that is, positive mental health, as measured with Mental Health Continuum‐Short Form [25]. We will use a linear mixed model on the data of the 3 measurements (baseline, directly after last treatment, and 26 weeks after baseline), comparing differences in the treatment effect. In addition, in order to assess subjective memory complaints, the Subjective assessment of memory impairment (subjective memory) assessment will be done at baseline, after the last treatment, and 26 weeks after baseline.

For the Percentual reduction of depressive symptoms, as measured with self‐rated PHQ-9 on each day using the PAiT protocol, compared to weekly reduction of depressive symptoms, as measured with PHQ-9 during standard 10 Hz rTMS we will use linear mixed models. Similarly, we will determine percent reduction of depressive symptoms, as measured with the clinically assessed HDRS‐17 before, during, and after treatment, as well as at the follow-up moments.

Relapse, at 6 and 25 weeks after treatment, defined as (1) sustained remission, that is, HDRS-17≤7, and (2) sustained response, that is, response at end of treatment maintained through week 6 and 25. During treatment phase (T2), we will conduct the HDRS-17 weekly for 6 weeks for both treatment arms. By doing this, using the chi-square test, we can compare the remission rate with PAiT after 6 weeks to 6 weeks of treatment with standard 10 Hz rTMS; this is of interest as patients allocated to PAiT only receive treatment for 1 week.

We will report the prevalence of side effects during and directly after treatment based on international recommendation [17]. We will establish the tolerability and side effects of PAiT and rTMS. We will use qualitative data collected while supporting the implementation of PAiT, to analyze health care system–, patient‐, and clinician‐related factors that influence the implementation of PAiT in clinical settings. We will use a 1-tailed paired *t* test or an ANOVA to compare patient-reported changes in mood 1 week after treatment (as measured with self-rated PHQ-9) with clinician-reported clinical impression (as measured with the Clinical Global Impression scale).

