## Methods

### Aim

The aim of the Dutch Depression Outcome Trial (D-DOTT) is to determine the cost‐effectiveness of PAiT versus standard daily 10 Hz rTMS in patients with TRD, who did not respond to 2 or more evidence‐based treatments, using an adequately powered RCT.

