#### Secondary Outcomes

In addition to the primary outcomes, secondary outcomes will be assessed to provide a more comprehensive understanding of the effectiveness and impact of rTMS/PAiT. First, an economic evaluation based on the general principles of a cost‐effectiveness (utility) analysis, which will be performed alongside the intervention by comparing patients treated with PAiT with those receiving standard 10 Hz rTMS. In addition, societal costs and health consumption will be assessed for the economic evaluation at baseline and 7, 12, and 26 weeks after baseline. We will use health‐related quality of life determined with the EQ‐5D‐5L and health care use or costs, patients’ and their family’s out‐of‐pocket costs, and productivity losses owing to absenteeism measured with the Trimbos Institute and Institute for Medical Technology Assessment Cost questionnaire for Psychiatry [24]. Second, patient‐reported outcome measures will be recorded, that is, positive mental health, as measured with Mental Health Continuum‐Short Form [25] and subjective memory loss. Third, percentage reduction of depressive symptoms will be measured with self‐rated 9-item Patient Health Questionnaire (PHQ-9) on each treatment day and the HDRS‐17. Fourth, relapse will be measured at 6 and 25 weeks after treatment. Relapse was defined as an HDRS‐17 total score of ≥15 for 2 consecutive assessments separated by 5 to 15 days or hospitalization for depression. Fifth, we establish tolerability of the treatment and side effects of PAiT and rTMS [9]. Sixth, we will identify health care system–, clinician‐, and patient‐related factors that influence the implementation of PAiT were identified to inform the development of an implementation plan. Seventh, we will compare patient-reported changes in mood 1 week after treatment (as measured with self-rated PHQ-9) with clinician-reported clinical impression (as measured with Clinical Global Impression [23]).

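### Baseline adjustment of QALYs and costs hangs on an undefined look at baseline balance, which leaves chance imbalance in the incremental QALY and gives up precision

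*Protocol article*

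**What the plan says.** The protocol article, under Secondary Study Parameters in the Statistical Analyses section, sets two steps for the economic evaluation. First: "A baseline analysis will be performed to examine the comparability of groups at baseline in terms of costs and outcomes". Then: "If necessary, the methods will be applied to control for differences in baseline", with a literature reference for the methods. It states no criterion for when adjustment is needed.

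The same section defines what is affected. "The outcome measure for the cost‐utility analysis will be quality-adjusted life years", from the EQ-5D-5L with Dutch utility weights, and the ICER "will be computed to obtain the incremental costs per quality-adjusted life years gained". Uncertainty comes from 5000 nonparametric bootstraps. Secondary Outcomes places the cost and health consumption measurements "at baseline and 7, 12, and 26 weeks after baseline".

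Two other places bear on the point. Randomization is stratified by treatment center only, so baseline utility and costs are not balanced by design. Relevance for Practice promises control for machine or site, but no section commits to adjusting for baseline utility or baseline costs. The Aim section says that the purpose of the trial "is to determine the cost‐effectiveness of PAiT versus standard daily 10 Hz rTMS in patients with TRD".

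**The concern.** A patient's baseline utility is the first point of the QALY curve and is correlated with every later point. It is therefore a strong prognostic covariate for the QALY, and this is known before any data are seen. Whether the two arms happen to look alike at baseline adds nothing to that argument.

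Making the adjustment depend on how the baseline table looks has three consequences:

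- Any imbalance judged too small to act on stays in the incremental QALY.
- The precision that adjustment would bring is lost whenever the arms look similar.
- An undefined judgement, made after the data are seen, decides which estimator produces the ICER denominator.

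This deserves attention because cost-effectiveness is the stated aim, while the sample size was derived for remission and not for QALYs or costs.

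**Working it through.** **The plan's own figures.** The economic evaluation has no size calculation, so only the trial's N can be reproduced. With 55% versus 25% remission, two-sided α 0.05, power 0.80 and pooled variance, n per arm = [1.960·√(2·0.40·0.60) + 0.842·√(0.55·0.45 + 0.25·0.75)]² / 0.30² = 40.7, so 41 per arm and 82 in total. Then 82 × 1.32 = 108.2, so 108, or 54 per arm. Both stated figures reproduce.

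**Assumptions not in the article.** Utility SD 0.20 (range 0.20 to 0.30). The same correlation ρ between any two visits (compound symmetry), at 0.3, 0.5 or 0.7. EQ-5D-5L measured at weeks 0, 7, 12 and 26; the article states this schedule for costs and health consumption only. No loss to follow-up.

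**Step 1: QALY weights.** The trapezoid rule gives weights in years of 3.5/52, 6/52, 9.5/52 and 7/52, which sum to 0.5. Baseline carries 3.5/52 = 0.067 and the later visits together 22.5/52.

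**Step 2: ordinary chance imbalance.** The SE of the baseline difference = 0.20·√(2/54) = 0.038.

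**Step 3: shift in the incremental QALY.** The slope of QALY on baseline utility is b = (3.5 + 22.5ρ)/52, and the shift is b × 0.0385.

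**Step 4: standard error.** Var(QALY)/SD² = (1−ρ)·Σw² + ρ·0.5², with Σw² = (3.5² + 6² + 9.5² + 7²)/52² = 187.5/2704 = 0.0693. The correlation of baseline utility with the QALY is r = b/√[Var(QALY)/SD²]. Adjustment multiplies the SE by √(1−r²).

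| ρ | b | Shift for a 1-SE imbalance | r | SE unadjusted | SE adjusted | Reduction |
|---|---|---|---|---|---|---|
| 0.3 | 0.197 | 0.0076 | 0.56 | 0.0135 | 0.0112 | 17% |
| 0.5 | 0.284 | 0.0109 | 0.71 | 0.0154 | 0.0108 | 30% |
| 0.7 | 0.370 | 0.0142 | 0.84 | 0.0170 | 0.0093 | 45% |

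Putting the between-visit ρ itself into √(1−ρ²) would give only 5%, 13% and 29%. That is the wrong correlation, because the QALY contains baseline and averages several visits.

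**Step 5: a yardstick.** The article gives no expected QALY gain. Assume 0.25 utility per remission. The difference is then (0.55 − 0.25) × 0.25 = 0.075 at each follow-up visit, and the QALY gain is 0.075 × 22.5/52 = 0.032. The shifts in the table are about 23%, 34% and 44% of it.

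**Step 6: sensitivity.** The shifts scale with the SD. At 0.30 they are 0.0114, 0.0164 and 0.0214. With 41 per arm and SD 0.20 they are 0.0087, 0.0125 and 0.0164. The percentage reductions in SE depend on neither.

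**Step 7: one possible reading of the condition.** Suppose adjustment were applied only when the baseline difference had p < 0.05 (an assumption; the article names no test). With SD 0.25 and 54 per arm, differences up to 1.96 × 0.25·√(2/54) = 0.094 would stay unadjusted. In 40,000 simulated trials with the slope treated as known, the SD of the estimated incremental QALY at ρ = 0.3, 0.5 and 0.7 was:

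- never adjusting: 0.0170, 0.0193, 0.0212
- adjusting conditionally: 0.0162, 0.0178, 0.0190
- always adjusting: 0.0140, 0.0135, 0.0116

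The share of the available gain that is lost is (0.0162 − 0.0140)/(0.0170 − 0.0140) = 73%, and likewise 74% and 77%.

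**Costs.** The article gives no cost SD and no correlation, so no figure can be produced.

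**The case against.** The strongest reply is that chance imbalance is ordinary sampling error. The unadjusted QALY difference is unbiased over randomizations, a one-SE baseline imbalance moves it by only 0.56 to 0.84 of its own SE, and the bootstrap and acceptability curve already carry that uncertainty. This stands, so the rule should not be called a source of systematic bias. It does not remove the loss of precision. Nor does the bootstrap reflect the choice between estimators unless that choice is repeated in each replicate.

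Three stronger readings are tempting and are not supported:

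- A reader might infer that the rule misses most harmful imbalances. That needs a trigger such as a significance test, and the article names none. The cited methods reference is not shown, and a fuller analysis plan might act on small differences. Step 7 is one scenario only.
- A reader might infer that the cost-effectiveness answer could change. No incremental cost or willingness-to-pay value is available to test this, and the one-SE shifts above, up to 0.021 at SD 0.30, all leave the illustrative 0.032 gain positive.
- A reader might carry the QALY argument over to costs unchanged. Baseline costs come from a 3-month recall before treatment and are not part of follow-up costs. Only their prognostic value argues for adjustment, and its size is unknown.

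It is also fair to say that the economic evaluation is listed as a secondary outcome and that an article leaves detail to fuller documents. But the look-then-adjust condition is the article's own commitment, not an omission, and a plan that follows it inherits it.

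**Conclusion.** The point holds as a free improvement, not as a flaw that invalidates the economic evaluation. The wording is certain: adjustment is conditional, without a criterion, and nothing elsewhere makes it unconditional. The consequences are chance imbalance left in the estimate when no adjustment is made, lower precision, and an estimator settled after the data are seen.

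Their size rests on the assumed utility SD, correlations and EQ-5D schedule. Of these, the gain in precision is the firmer result, since it depends only on the correlation and the visit schedule. The comparison with a gain of about 0.03 also depends on the assumed utility per remission and is illustrative. The quantified claim covers QALYs only.

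**What to change.** Remove the condition. State that, whatever the observed balance, incremental QALYs are estimated by regression on arm, baseline EQ-5D utility and center, and incremental costs by regression on arm, baseline costs and center. Fit both models within each bootstrap replicate, after the nested imputation. Seemingly unrelated regression is one way to fit the pair, but not the only one. Keep the baseline comparison as description only.

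The cost is a change of wording in the article's successor documents or the analysis plan. Baseline costs are already scheduled, and the planned comparability check presupposes baseline outcomes, so no new data are needed. The last posttreatment assessments are expected in January 2027, which leaves time to fix this before analysis.
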